# Evaluation on immediate analgesic efficacy and safety of Kai-Hou-Jian spray (children’s type) in treating sore throat caused by acute pharyngitis and tonsillitis in children: study protocol for a randomized controlled trial

**DOI:** 10.1186/s13063-021-05148-1

**Published:** 2021-03-18

**Keywords:** Acute pharyngitis/tonsillitis, Kai-Hou-Jian spray, Randomized controlled trial, Sore throat, Traditional Chinese medicine

## Abstract

**Background:**

Acute pharyngitis and tonsillitis are common respiratory diseases for which children seek medical care. Their main clinical manifestation is sore throat which interferes with patients’ quality of life. However, there is no proven effective or safe method to treat it. It is necessary to find an excellent strategy to reduce sore throat and reduce the burden of acute illness. We designed the randomized controlled trial with the characteristics of traditional Chinese medicine (TCM) to determine the clinical positioning of Kai-Hou-Jian spray (children’s type) (KHJS) through evidence-based research. This trial aims to evaluate the immediate analgesic efficacy of KHJS on sore throat caused by acute pharyngitis and tonsillitis (wind-heat syndrome/heat exuberance in lung and stomach syndrome) in children and to observe its safety.

**Methods/design:**

This is a prospective, multicenter, randomized, double-blind, parallel-group, placebo-controlled trial. It will include 240 children with acute pharyngitis/tonsillitis from 7 study sites across China. All participants are randomly assigned to two parallel treatment groups, one with KHJS and the other with placebo sprays, for 5 consecutive days. The primary outcome is the time of analgesic onset. Secondary outcomes include duration of analgesic effect, area under time curve of 0–3 h Wong-Baker FACES Pain Rating Scale (WBS) score (AUC0-3 h), rate of analgesic onset, rate of disappearance of sore throat, changes of WBS score (in days), effective rate of pharyngeal signs, and effective rate of TCM syndrome. The incidence of adverse events during the trial is the primary safety outcome. In addition, vital signs and laboratory tests before and after medication are monitored.

**Discussion:**

To our knowledge, this will be the first clinical trial to explore the immediate analgesic efficacy of a Chinese patent medicine spray for acute pharyngitis/tonsillitis induced sore throat in children in a multicenter, randomized, double-blinded, parallel-group, placebo-controlled manner. Not only might it prove the efficacy and safety of KHJS in the treatment of sore throat caused by acute pharyngitis/tonsillitis in children, but it might also provide evidence for the treatment of acute sore throat with Chinese herbal medicine.

**Trial registration:**

A multicenter, randomized, double-blind, very low-dose, parallel controlled trial for the immediate analgesic effect and safety of Kai-Hou- Jian spray (children's type) in the treatment of sore throat caused by acute pharyngitis and tonsillitis in children. Chinese Clinical Trial Registry ChiCTR2000031599. Registered on 5 April 2020

**Supplementary Information:**

The online version contains supplementary material available at 10.1186/s13063-021-05148-1.

## Background

Acute pharyngitis and tonsillitis are common respiratory diseases for which children seek medical care and they are sometimes referred to together as acute sore throat [1].Seventy to 95% of children with acute sore throat are caused by virus, mainly respiratory virus, while 15–30% are caused by bacterial, such as β hemolytic group A *Streptococcus* [2–4]. Systemic analgesia or soothing measures such as gargling with warm salt water are often used to treat sore throat caused by acute pharyngitis/tonsillitis, but the relief is short and some systemic analgesic agents have been shown to have some adverse effects. For children with bacterial pharyngitis/tonsillitis, antibiotic therapy should be added to prevent complications and the spread of infection, but antibiotics are less effective in reducing pain [5, 6]. Sore throat seriously affects the life quality of children and their families, so it is necessary to find an excellent strategy to reduce symptoms and reduce the burden of acute illness.

Kai-Hou-Jian spray (children’s type) (KHJS), which has been on the market for more than 10 years, is a Chinese patent medicine produced by Guizhou Sanli Pharmaceutical Co., Ltd. (Guizhou, China). It has been authorized by the China State Food and Drug Administration (Drug Approval number 20025142) and is commonly used in the clinical treatment of pharyngitis, tonsillitis, sore throat, stomatitis, and so on. The prescription of KHJS comes from Miao medicine experience in Guizhou. It is mainly composed of *Ba Zhao Jin Long [Ardisia crispa (Thunb.) A.DC.]*, *Shan Dou Gen [sophorae tonkinensis radix etrhizoma]*, *Chan Tui [cicadaeperiostracum]*, *Bo He Nao [l-menthol]*. In the theory of traditional Chinese medicine (TCM), KHJS have the functions of clearing heat and removing toxicity and relieving swelling and pain. The pharmacodynamic test showed that KHJS could inhibit the auricular inflammation of mice caused by xylene, relieve the fever of rats caused by typhoid and paratyphoid triple vaccine, and reduce the number of writhing of mice caused by acetic acid. In vitro antiviral and bacteriostatic tests showed that KHJS has a wide range of inhibitory effects on influenza A virus, Gram-positive bacteria, and Gram-negative bacteria [7]. According to the data, the incidence of adverse reactions of KHJS from 2017 to 2019 is < 0.01%, which belongs to the “very rare” category [8].

There have been previous studies in humans on the use of KHJS in the treatment of acute pharyngitis /tonsillitis, but there are some problems, such as too small sample size and not using double-blind methods. Moreover, these studies take the overall improvement of several TCM symptoms as the primary outcome, which is lack of objectivity and science to a certain extent [9, 10]. We designed this prospective, multicenter, randomized, double-blind, parallel-group, placebo-controlled trial to seek a proven effective and safe way to reduce the pain caused by acute pharyngitis /tonsillitis. The objective of this trial is to evaluate the immediate analgesic efficacy of KHJS on sore throat caused by acute pharyngitis /tonsillitis (wind-heat syndrome/heat exuberance in lung and stomach syndrome) in children, and to observe its clinical safety.

## Methods/design

This is a prospective, multicenter, randomized, double-blinded, parallel-group, placebo-controlled trial of KHJS versus placebo spray for acute pharyngitis/tonsillitis in children. Supported by ' Evidence-based study on the clinical location of KHJS '(NO.2018YFC1708106), Major Project ' Modernization of TCM ' of Ministry of Science and Technology of the People's Republic of China. In addition, it has been registered on the Chinese Clinical Trial Registry (ChiCTR2000031599). The study protocol is conducted in accordance with the Declaration of Helsinki, the code of Good Clinical Practice, and the guidelines of the International Conference on Harmonisation. Recruitment is scheduled to occur from June 2020 until December 2020. Figure 1 shows the flow chart of the trial.

**Fig. 1 Fig1:**
[figure not shown]
Study flow chart

### Patient population and setting

The diagnosis of acute pharyngitis/tonsillitis is made by a qualified pediatrician with reference to *Practical pediatric otolaryngology*, *Clinical pediatrics*, and *ZhuFutang practical pediatrics* [11–13]. It is mainly summarized as the onset of urgent, first dry pharynx, and then pharynx pain, pharynx or tonsil congestion, swelling or even suppuration, or accompanied by cervical lymph node enlargement, tenderness, as well as also accompanied by fever, headache, poor appetite, and other systemic symptoms. Syndrome differentiation standard of wind-heat syndrome/heat exuberance in lung and stomach syndrome of pharyngitis/tonsillitis is formulated according to the *Guidelines for the diagnosis and treatment of common diseases in traditional Chinese otorhinolaryngology* [14] and *Guidelines for the diagnosis and treatment of common diseases in pediatrics of traditional Chinese medicine* [15].

A total of 240 children of either sex, aged 4–12 years, will be enrolled from 7 study sites across China: (1) the First Teaching Hospital of Tianjin University of TCM, (2) Dongzhimen Hospital, Beijing University of Chinese Medicine, (3) Xiangya Hospital, Central South University, (4) Nanjing Children’s Hospital, (5) Tianjin Medical University General Hospital, (6) the First Affiliated Hospital of Hunan University of Traditional Chinese Medicine, and (7) Children’s Hospital of Chongqing Medical University.

#### Inclusion criteria

Clinical diagnosis of acute pharyngitis/acute tonsillitis;Wind-heat syndrome or heat exuberance in lung and stomach syndrome in TCM;Wong-Baker FACES Pain Rating Scale (WBS) score of sore throat with swallowing ≥ 4, body temperature < 38.5°C;Aged 4 to 12 years, can use WBS correctly;All patients (≥ 8 years old) and their guardians should sign the informed consent before entering the study, and children under 8 years old should sign the informed consent by their guardians.

#### Exclusion criteria

At the first diagnosis, the child’s condition is more serious, and he/she suffers from poor mental state, irritability, headache, or limb muscle pain, and needs antipyretic analgesics;Children or their parents/caregivers have difficulty understanding or cooperating with the use of WBS;Children with peritonsillar or retropharyngeal abscesses, infectious mononucleosis, measles, or scarlet fever;Children with severe primary diseases of heart, lung, liver, kidney, metabolism, hematopoietic, immune, nervous, and spiritual systems;Children with acute laryngitis, otitis media, bronchitis, pneumonia, and other complications;Allergic to components of KHJS, or antipyretic analgesics;Those who had taken acetaminophen, ibuprofen, or other antipyretic analgesic within 6 h before enrollment;Unfixed residence, children’s apparent inability to cooperate with the study, and other conditions deemed inappropriate by the researchers.

#### Withdrawal criteria

Children with severe complications;Children with no improvement or aggravation after 3 days of treatment;Children with anaphylaxis or serious adverse events who are judged by the physician to be discontinued;Children with poor medication compliance;Children who break blind procedure for a variety of reasons;Children participating in the randomization who have seriously violated the inclusion or exclusion criteria.Children who are unwilling or unable to continue the trial for a variety of reasons and request to withdraw from the trial.Lost to follow-up children who are not explicitly asked to withdraw from the trial but are no longer receiving experimental drug or testing.

#### Termination criteria

When a serious safety event occurs in the clinical trial.When it is found that there is a major error in the clinical trial protocol, or there is a serious deviation in the implementation of the protocol.In the course of the experiment, it is found that the experimental drug has poor therapeutic effect and no clinical application value.The ethics committee called for the trial to be suspended or terminated.The competent administrative department canceled this trial.

### Randomization, concealment, and masking

Randomization (1:1) will be stratified by study site, and the randomization list is generated by an independent statistician using SAS v 9.2. Two hundred forty children are divided into 40 blocks with the block size as 6. The documents of random process and randomization list will be enclosed in an opaque envelop. Participants, researchers, and coordinators together with statisticians were not aware of the allocation of the patient and remained unaware until trial completion. All study sites will also receive opaque envelopes containing the experimental drug’s website, login ID, password, instructions, security information, and treatment recommendations, which the researchers should open in an emergency.

In this trial, we use a very low dose (5%) of KHJS solution as a placebo spray. It contains 0.525 g/15 ml of crude herbs, while KHJS contains 10.05 g/15 ml crude herbs. Both the KHJSs and placebo sprays are manufactured by Guizhou Sanli Pharmaceutical Co., Ltd. with the same specification, appearance and flavor. These sprays are coded, packed, and labeled based on randomization list. Each center has an independent drug administrator responsible for the storage, distribution, recovery, and documentation of all experimental drugs.

### Interventions

All participants are randomly allocated to one of the two parallel treatment groups. Spray the pharyngeal region with KHJS or placebo spray in a dose of 5 sprays for ages 4 to 6 and 7 sprays for ages 7 to 12. Depending on the condition of the sore throat, the spray can be reused every 3 to 6 h, but not more than 8 times every 24 h. Treatment is planned for 5 consecutive days, but patients whose sore throat disappears may terminate treatment early.

### Concomitant treatments and forbidden medication

Children with indications of bacterial infection should be treated with antibiotics [16]. Antiviral chemicals are allowed if a child is infected with virus. Children with fever can adopt physical cooling measures such as cooling paste and warm water bath. Antipyretic analgesic should not be used until 3 h after the first dose. Other pharyngeal local medications or system medications with antipyretic detoxification effect are prohibited. All concomitant treatments or medication administered must be recorded carefully in case report form (CRF) and subject medical record, including the name, duration of administration, dosage, and cause of administration. It is also necessary to determine whether concomitant medication affects the efficacy of experimental drug.

### Outcome measures

#### Primary outcome

The primary outcome is the time of analgesic onset. Analgesic onset is based on WBS score of sore throat (swallowing pain, same below) intensity, and defined as the reduction of WBS score ≥ 1 grade after the first dose. The WBS uses 6 different faces from smile to crying to describe the pain intensity of children aged 3 and above, from no hurt (0 point) to hurts worst (10 point), with a 2-point interval. It does not need specific cultural background, is easy to grasp, and has a good correlation with other commonly used scales [17, 18]. Children will be asked to swallow and to choose an expression to show how much their throat hurts now. In order to obtain the data of primary outcome, the children will be evaluated 12 times for WBS score (baseline and 5, 10, 20, 30, 40, 50, 60, 90, 120, 150, and 180 min after the first dose) by researchers in the hospital.

#### Secondary outcome

We will also collect data for the following additional outcomes: duration of analgesic effect, area under time curve of 0–3 h WBS score (AUC0-3 h), rate of analgesic onset, rate of disappearance of sore throat, changes of WBS score (in days), effective rate of pharyngeal signs, and effective rate of TCM syndrome.

The duration of analgesic effect, AUC0-3 h, and the rate of analgesic onset are all obtained from the WBS scores in first 3 h. The rate of analgesic onset will be evaluated at 30 and 60 min after the first dose. Rate of disappearance of sore throat will be evaluated at full 3 and 5 days. Disappearance of sore throat is defined as a reduction in WBS score to 0. Changes of WBS score will be evaluated at full 1, 2, 3, 4, and 5 days conducted at home by the child’s parents/caregiver.

The data of effective rate of pharyngeal signs and effective rate of TCM syndrome are collected by the symptoms and signs scale based on TCM syndromes (Table 1) compiled according to some guidelines [14, 15, 19, 20]. Both of the effective rate of pharyngeal signs and effective rate of TCM syndrome will be evaluated at baseline and full 5 days. Effectiveness of pharyngeal signs means the reduction of total score range from baseline to finish ≥ 50%. The effectiveness of TCM syndrome is defined as the decline rate of TCM syndrome score ≥ 50% after medication.

**Table 1 Tab1:** Symptoms and signs scale based on TCM syndromes

**TCM main syndrome**		**Score grading**					
		**0**	**1**	**2**	**3**	**4**	**5**
Sore throat		WBS 0	WBS 2	WBS 4	WBS 6	WBS 8	WBS 10
**TCM minor syndrome**		**Score grading**					
		**0**	**1**	**2**	**3**		
**Wind-heat syndrome**	Fever	No	37.3–38 °C	38.1–38.9 °C	≥ 39 °C		
	Headache	No	Yes				
	Afraid of the wind	No	Yes				
	dryness and heat of pharyngeal	No	Yes				
	Cough or with yellow sputum	No	Yes				
**Heat exuberance in lung and stomach syndrome**	Fever	No	37.3–38 °C	38.1–38.9 °C	≥ 39 °C		
	Cough or with yellow sputum	No	Yes				
	Thirst	No	Yes				
	Bad breath	No	Yes				
	Abdominal distension	No	Yes				
	Dry stool	No	Yes				
	Yellow-colored urine	No	Yes				
**Pharyngeal signs**		**Score grading**					
		**0**	**1**				
**Wind-heat syndrome**	The pharyngeal mucosa is bright red and swollen	No	Yes				
	Tonsil is red and swollen, without pus	No	Yes				
	The lymph nodes are swollen and painful under the jaw	No	Yes				
**Heat exuberance in lung and stomach syndrome**	The pharyngeal mucosa is red and swollen	No	Yes				
	Tonsil is red and swollen, or companion pus point	No	Yes				
	The lymph nodes are swollen and painful under the jaw	No	Yes				

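### Scored literally, the wind-heat tonsil item in Table 1 drops to 0 when pus appears, so some children who worsen would be classed as effective on pharyngeal signs

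*Protocol article*

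**What the plan says.** Table 1 (Outcome measures, Secondary outcome) gives three pharyngeal signs per syndrome, each scored No = 0 or Yes = 1. For wind-heat syndrome they are:

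- "The pharyngeal mucosa is bright red and swollen"
- "Tonsil is red and swollen, without pus"
- "The lymph nodes are swollen and painful under the jaw"

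For heat exuberance in lung and stomach syndrome, the tonsil item is instead "Tonsil is red and swollen, or companion pus point".

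The responder rule, in the same section, reads: "Effectiveness of pharyngeal signs means the reduction of total score range from baseline to finish", with a threshold of at least 50%. On timing it says: "Both of the effective rate of pharyngeal signs and effective rate of TCM syndrome will be evaluated at baseline and full 5 days".

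The article does not say how to score a wind-heat child whose tonsil later shows pus, whether that child moves to the other item list, or whether new pus rules out being effective.

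**The concern.** The wind-heat tonsil item combines two conditions: redness with swelling, and absence of pus. That suits a description that tells one syndrome from another at entry. Used as a change score it fails, because the item can return to 0 in two opposite ways: the tonsil heals, or it suppurates. The total treats both as one point of improvement.

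Pus lies within the disease under study. The diagnostic summary in Patient population and setting includes "pharynx or tonsil congestion, swelling or even suppuration", and the exclusion criteria name peritonsillar and retropharyngeal abscess but not tonsillar pus. With a total of 0 to 3 and a 50% cut, one item can decide the classification. At stake is whether a named efficacy rate counts some worsened children as successes.

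**Working it through.** The article gives no figure for this outcome that could be reproduced, so the check applies its scoring rule to every possible sign pattern.

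**Inputs.** From Table 1: three 0/1 wind-heat items (mucosa, tonsil, nodes), total 0 to 3. From Secondary outcome: effective if (baseline − day 5) / baseline ≥ 50%. Scenario: tonsil red and swollen without pus at baseline (item = 1), pus at day 5. Literal wording scores the tonsil 0 at day 5; a pus-inclusive item would score it 1.

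**Step 1. Only the tonsil changes.**

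| Signs at baseline | Literal total | Literal reduction | Class | Pus-inclusive reduction |
|---|---|---|---|---|
| Tonsil only | 1 to 0 | 1/1 = 100% | effective | 0% |
| Tonsil + mucosa | 2 to 1 | 1/2 = 50% | effective | 0% |
| Tonsil + nodes | 2 to 1 | 1/2 = 50% | effective | 0% |
| All three | 3 to 2 | 1/3 = 33% | not effective | 0% |

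In three of the four patterns, progression to pus alone produces a responder.

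**Step 2. All three signs at baseline, and one of the other two clears.** Literal: 3 to 1, (3 − 1)/3 = 67%, effective. Pus-inclusive: 3 to 2, (3 − 2)/3 = 33%, not effective.

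**Step 3. Another sign appears.** Tonsil + mucosa at baseline, with nodes newly positive at day 5: literal 2 to 2 = 0%, not effective. The new item cancels the artefact.

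**Step 4. All combinations.** The other two items have 4 baseline states and 4 day-5 states, so 16 combinations. Literal scoring classes 10 as effective and pus-inclusive scoring classes 3, so 10 − 3 = 7 are effective only because of the wording. These are counts of patterns, not probabilities, since the article does not say how common each pattern is.

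**Step 5. What a pus-inclusive item leaves open.** The 3 remaining combinations are those where at least one other baseline sign is present and every such sign clears while pus appears: baseline totals of 2, 2 and 3, each ending at 1, give 50%, 50% and 67%. Such a child still counts as effective, because a 0/1 item that covers pus shows no change rather than worsening. A changed item is therefore not enough without an explicit rule for new pus.

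**The case against.** The strongest reply is that the harm depends on a strict reading of one translated table cell. The no-pus phrase could be meant only to identify the syndrome, with redness and swelling as the scored sign, and the article says researchers will be trained in evaluating the indicators. That is possible, but the text does not say it. The lung-and-stomach item admits pus explicitly, so the table distinguishes the two states on purpose, and a rater at any of the seven sites who follows the wording would score No.

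A second reply is that such children may never reach a day-5 score. The withdrawal criteria cover those who are no better or worse after three days, antibiotics are allowed where bacterial infection is indicated, and carrying the last value forward is stated only for the primary outcome. This stands in part: the number affected would be smaller. But withdrawal assigns no non-effective score, does not by itself take a child out of the full analysis set, and does not reach pus that appears later.

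A reader might also infer that the two tonsil items contradict each other. They do not. The lists are separate by design and each child is compared with their own baseline. The fault lies in the direction of change within the wind-heat list.

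**Conclusion.** The point holds as a scoring defect of limited reach. Followed as written, Table 1 classes a wind-heat child with new pus and otherwise unchanged signs as effective when the baseline total is 1 or 2, but not when it is 3. This assumes literal scoring, the tonsil item positive at baseline, and a day-5 assessment. It touches one of three sign items in one of seven secondary outcomes, for one syndrome. The primary outcome is unaffected.

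Two stronger readings are tempting and unsupported. One is a number of misclassified children per arm. The article gives neither the share of wind-heat children nor the rate of progression to pus, and a count of all progressors would be too high, since some have three baseline signs or gain a new one. The other is that the artefact favours KHJS. The trial is randomized and double-blind with the same scale in both arms. With equal progression, both arms could gain false responders; if KHJS prevented suppuration, the placebo arm would gain more and the effect would be understated. The article does not settle the direction. This is a minor correction, worth making because it is so cheap.

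**What to change.** For the outcome score, use one tonsil item for both syndromes at baseline and day 5: red and swollen, with or without pus. Keep the no-pus qualifier only in the syndrome differentiation at entry. Add one sentence to the responder definition: a child with new pus at day 5 is classed as not effective, whatever the total.

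This changes one line of Table 1, the responder definition and the case report form's scoring note. It needs no new assessment and alters no treatment rule. The cost is a small departure from the wording of a scale compiled from cited guidelines, which should be stated when the outcome is reported.
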